### Setting

The MicUTI study is conducted in a primary care research network based in the German Federal State of Bavaria, the Bavarian Practice-Based Research Network (BayFoNet). Three out of the five university departments part of the BayFoNet participate in MicUTI. These are the Department of General Practice of the University Hospital Würzburg (hereafter abbreviated as UKW), which is the trial coordinating centre, the Institute of General Practice of the Friedrich-Alexander Universität Erlangen-Nürnberg (hereafter abbreviated as FAU) and the Institute of General Practice and Family Medicine of the Ludwig-Maximilians University Hospital Munich (hereafter abbreviated as LMU), who collaborate in the recruitment of study sites and data collection. An accompanying mixed-methods process evaluation assesses the implementation of this trial into the BayFoNet and further investigates its feasibility and acceptability to general practice teams. Details of the process evaluation study are published elsewhere.^28^

### Recruitment of study sites

The UKW and the FAU will recruit 20 general practices located in the Federal State of Bavaria (Würzburg and Erlangen and surrounding areas) to participate in the trial through postal invitations, institutional advertisements such as newsletters and website announcements and public conferences with GP practice teams.

### Randomisation of study sites

General practices participating in the trial (hereafter: study sites) will be asked to provide the number of consulting patients over the last year to determine practice size. Study sites of larger size are foreseeably able to recruit more patients for the duration of the trial, so that practice size will be balanced between the two arms (each with 10 practices) using minimisation.^29^ The minimisation algorithm is centrally programmed in Python by the study statistician. To mask the trial statistician (GB) to intervention/control assignments, the minimisation algorithm will be executed by the trial’s statistical consultant based at the Technical University of Munich (AH), who is not involved in the conduction of the trial. Intervention/control assignments of practices will be communicated to the UKW and the FAU, who then will communicate their allocation to the study sites. To minimise selection bias, study sites were identified for inclusion in the trial prior to randomisation.

### Patient recruitment/enrolment

#### Identification of women eligible for inclusion

At presentation, at all study sites, medical assistants will consecutively approach all adult women presenting with two or more symptoms suggestive of acute uUTI (dysuria, frequency, urgency, nocturia, lower abdominal pain) to identify trial participants. To ensure consecutive enrolment and control for selection bias, all potential participants will be approached and listed in paper-based anonymous patient pre-screening logs at each study site. Interested women will be asked to complete the validated symptom questionnaire UTI-SIQ-8^27^ and will be provided with a comprehensive patient information leaflet that details trial procedures in lay language.

The GP will exclude from participation all women with one or more of the following:

Signs of a complicated UTI (anamnesis of fever, chills or flank pain).Clinically relevant immunosuppression (ie, current use of any immunosuppressive therapy, congenital or acquired disorders of immunity).Acute or chronic functional or anatomical variations in the urinary tract except for chronic kidney failure with a glomerular filtration rate (eGFR) >45 mL/min.Permanent bladder catheter or use of bladder catheter within the past 2 weeks.UTI within the past 2 weeks.Use of any antibiotic within the past 2 weeks.Accommodation in a nursing home or hospital stay within the past 2 weeks.Severe neurologic, psychiatric illness, severe dementia or severe substance use disorder.Other severe diseases.Being unable to understand the informed consent or to complete the patient diary.Known pregnancy.

Women who consent will be asked to sign an informed consent form, which also contains data protection regulations.

### Intervention arm

GPs whose practice is allocated to the intervention will have their management guided by POCTs, namely phase-contrast microscopy and urinary dipsticks, for all patients consenting to participation.

#### Point-of-care tests

Medical assistants will perform microscopy using phase-contrast microscopes (‘Primostar’, Carl Zeiss Suzhou, Suzhou, China) to examine 7 µL of clean-catch mid-stream urine (MSU) without prior centrifugation at 400× magnification in a precision counting chamber (Fast-Read 102 slides, Biosigma S.r.l., Cona (VE), Italy) to detect bacteria. A test will be considered positive if more than a few bacteria of the same shape (rod or cocci) or if many bacteria of different shapes (rod and cocci) are detected per high power field.^30^

Urinary dipstick analysis will be performed using COMBUR5-Test (Roche Diagnostics GmbH, Mannheim, Germany) to examine 50 mL MSU to identify erythrocytes. In accordance with the manufacturer instructions, the COMBUR5-test strip will be dipped in the urine sample for about 1 s, wiped against the rim of the vessel to remove excess urine and read manually after 60 s by comparing the colour of the detection pad of the strip with the colour scale on the test strip vial. A positive test result is defined as the colour change of the strip corresponding to 1+erythrocytes or greater.

All the analyses will be conducted immediately after the MSU specimen collection at each study site.

#### Training of study sites in trial procedures

Medical assistants will be provided with ad hoc training to approach potentially eligible women consecutively, and to perform POCTs according to the study protocol by dedicated staff. Training will be delivered face-to-face prior to patient recruitment over a 3-hour session (baseline session), as well as 3 months after the start of patient recruitment (refresher session), following the principles of competency-based medical education.^31^ The baseline training session will entail the following: (1) Guideline knowledge on UTI in women to allow medical assistants to identify potentially eligible women in each study site; (2) POCT training to perform and interpret the results of phase-contrast microscopy and urinary dipsticks according to the study protocol. The knowledge and skills gained, and their retention, as well as the feasibility and the acceptability of the training sessions and the use of phase-contrast microscopes in daily practice, will be assessed through a questionnaire addressed to medical assistants before, immediately after, and 3 months after the training session and through face-to-face semi-structured interviews, 3 months after the training session. Interviews will be conducted following a pre-planned interview-guide informed by the Consolidated Framework for Implementation Research.^32^ Practical tests at the microscope directly after the training session and after 3 months will assess each medical assistant’s acquisition and retention of practical skills.

#### Point-of-care test guided treatment algorithm

Based on the prognostic and moderating effects on treatment outcomes of erythrocytes and bacteria in urine,^13^ GPs will be encouraged to apply the following treatment algorithm (figure 1) to consenting women, taking their preferences into account:

If POCTs are positive for bacteria by microscopy and/or for erythrocytes by dipsticks, the GP issues, at their own clinical judgement, a delayed or immediate prescription for an antibiotic. In the MicUTI intervention, a delayed prescription can be issued by GPs, at their discretion, in either way: the prescription is handed out to the patient with the advice to redeem it only if symptoms do not improve or worsen in 48 hours, or it is withheld in the GP practice. It can be handed out if the patient presents again with issues.If POCTs are negative for bacteria and erythrocytes, the GP advises for self-help remedies according to national guidelines and to do without antibiotics.^33 34^

**Figure 1 F1:**
[figure not shown]
Treatment algorithm in the intervention arm. GP, general practitioner; uUTI, uncomplicated urinary tract infection.

#### Data collection

##### Baseline

Baseline data will be collected during routine consultation. The medical assistant records microscopy and dipstick test results, clinical features and the GP’s management decisions, including antibiotics prescribed on a baseline paper-based case report form (CRF). In addition, the medical assistant inoculates a dipslide (see paragraph ‘microbiological analyses’) to be sent via post on the same day to the central research laboratory based at the Institute of Hygiene and Microbiology of the Julius-Maximilians-University of Würzburg (IHM) for microbiological analysis.

##### Follow-up

Follow-up data will be collected through a self-directed patient diary, follow-up telephone calls on day 28 from inclusion and follow-up in the GP practice in case of reconsultation. In addition, an electronic medical records (EMR) review will also be performed to double-check for missing follow-up data.

**Patient diary:** Women will be asked to rate their daily symptoms and impairment due to UTI on a scale from 1 (no symptoms/impairment at all) to 5 (very strong symptoms/impairment) and to write down the antibiotics taken in a diary for at least 7 days (or up to 14 days if symptoms last longer).^27^ Enough space in the diary is left for women to take extra notes. They will be asked to return the completed diary to their GP practice using a pre-paid envelope or in person. Research nurses at the FAU and the LMU will perform telephone calls on days 2–4 from inclusion to remind enrolled women to fill out and return the diary.

**Follow-up telephone calls:** Calls will be performed by research nurses at the FAU and the LMU on day 28 from inclusion to collect data on symptoms, antibiotic use due to UTI, recurrences and reconsultations with UTI symptoms.

**Follow-up in the GP practice:** Every time a woman reconsults for UTI within 28 days, the GP records clinical features, management decisions and antibiotics prescribed on follow-up paper-based CRFs.

**Electronic medical records review:** Researchers from the UKW and the FAU will perform outreach visits at the end of the patient recruitment (6 months) in each of the study sites. Paper-based CRFs will be collected, and data will be controlled for completeness. To double-check data entries for accuracy and completeness, EMRs will be enquired on reconsultations with UTI symptoms, recurrences, antibiotics prescribed due to UTI and upper UTI until day 28 from inclusion.

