#### Control arm–usual care

Practices in the control arm will not necessarily have their management guided by POCTs. They will perform usual care. The treatment decision is usually based on symptoms. Dipsticks for detecting erythrocytes, leucocyte esterase or nitrites can be added in case of diagnostic uncertainty.^33^ Procedures are the same as those outlined above, except for POCTs: microscopy only pertains to the intervention arm.

Table 1 and figure 2 summarise trial procedures.

**Table 1 T1:** Schedule of Microscopy in Urinary Tract Infections trial procedures according to the Standard Protocol Items: Recommendations for Interventional Trials guideline^40^

Time point (day 0=patient enrolment) procedures	<0	Day 0 Baseline	Day 1–7	Day 28	End of patient enrolment*
Enrolment:					
Practice recruitment	X				
Randomisation	X				
Allocation	X				
Training	X				
Screening for potential inclusion		X			
Formal eligibility assessment		X			
Intervention:					
Baseline consultation†		X			
POCTs‡		X			
Urine sent to laboratory†		X			
Assessments:					
Practice size	X				
Paper-based CRF§		X			
Patient diary¶			X		
Follow-up telephone calls				X	
EMR review**					X

*End of patient enrolment in each practice.

†Applies to intervention and control arm practices.

‡Applies only to intervention arm practices.

§In case of reconsultation for UTI on days 1–28, paper-based follow-up CRFs are used.

¶Follow-up on days 1–7 or up to day 14 if symptoms last longer or recur.

**Follow-up on days 1–28 (CRF completeness and accuracy check).

CRF, case report form; EMR, electronic medical records; POCT, point-of-care test; UTI, urinary tract infection.

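### The site visit for CRF collection and EMR review is timed at the close of enrolment, yet must cover each woman to day 28; no lag is stated

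*Protocol article*

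**What the plan says.** In the Follow-up section, the paragraph on electronic medical records review says that researchers from two of the centres "will perform outreach visits at the end of the patient recruitment (6 months) in each of the study sites". Two tasks belong to that visit. The first is CRF retrieval: "Paper-based CRFs will be collected, and data will be controlled for completeness". The second is the record search: "EMRs will be enquired on reconsultations with UTI symptoms, recurrences, antibiotics prescribed due to UTI and upper UTI until day 28 from inclusion".

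Table 1 (under Control arm–usual care) puts the EMR review in its last column, which a footnote explains as "End of patient enrolment in each practice". A second footnote gives the coverage of the review as days 1 to 28.

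The same section describes the other follow-up sources:

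- **Diary:** symptoms and antibiotics taken, for at least 7 days and up to 14 if symptoms last longer.
- **Telephone call:** "Calls will be performed by research nurses at the FAU and the LMU on day 28 from inclusion to collect data on symptoms", and also antibiotic use due to UTI, recurrences and reconsultations.
- **Practice follow-up:** "Every time a woman reconsults for UTI within 28 days, the GP records clinical features", together with management decisions and antibiotics prescribed, on a paper CRF.

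The record review is introduced as an addition to these: "an electronic medical records (EMR) review will also be performed to double-check for missing follow-up data".

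**The concern.** A woman enrolled in the last 28 days of a practice's recruitment has not reached day 28 when recruitment closes. A visit at that moment cannot search her record to day 28, and it cannot collect a reconsultation CRF that has not yet been written. The timing and the coverage are each stated twice, in the text and in Table 1. This is therefore a conflict between stated rules, not a detail left to a fuller document.

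The secondary endpoints that lean on the visit are:

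- **Upper UTI within 28 days.** Among the follow-up sources, only the EMR review names it; the listed content of the call does not. It bears on the trial's aim of reducing antibiotic use safely.
- **Number of antibiotic prescriptions and defined daily doses within 28 days.** The call asks about antibiotic use, and the diary stops at day 7 to 14. After that, prescription detail comes from the follow-up CRFs and the record.
- **Back-up for missing follow-up.** The record review is the stated check where other data are missing, so a gap there matters most for women whom the call does not reach.

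**Working it through.** The protocol gives no figure on this point, so there is none to reproduce. Its one precision statement (the confidence interval width for complete follow-up) does not enter the calculation.

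**Inputs from the document**

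- Follow-up window: 28 days from inclusion (Follow-up; Table 1).
- Enrolment period: 6 months (Design; Sample size considerations).
- Planned sample: 200 women, on average 10 in each of 20 practices (Sample size considerations).

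**Assumptions, not in the document**

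- Accrual is uniform. The article gives no enrolment curve; it says only that encounters show slight seasonal fluctuation.
- 6 months = 182.5 days.
- The visit falls on the last day of enrolment.

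**Step 1. Women short of day 28 at the visit.** Share = 28/182.5 = 15.3%. Of 200 women: 0.153 × 200 = 30.7, about 31. Per practice of 10: about 1.5. With 180 or 183 days in place of 182.5, the share is 15.6% or 15.3%, still about 31 women.

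**Step 2. Women with no part of days 15–28 in the record.** These are the women enrolled in the last 14 days: 14/182.5 = 7.7%, or about 15 of 200.

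**Step 3. Share of 28-day person-time not yet in the record or CRFs.** The women in step 1 lack 14 of 28 days on average: 0.153 × 14/28 = 7.7%.

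**Step 4. Share of day 15–28 person-time not yet in the record or CRFs.** Half of the women in step 1 have none of the 14 days observed. The other half have 7 on average. The mean observed is 3.5 of 14 days, so 75% is missing: 0.153 × 0.75 = 11.5%.

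**Step 5. Range over the visit date and the enrolment period.**

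- Visit at least 28 days after the last inclusion at the practice: 0 women.
- Longer enrolment: Trial status gives recruitment from June 2023 to a planned end in April 2024. If a practice enrolled for that whole span, taken at its longest as 1 June to 30 April (335 days), the share would be 28/335 = 8.4%, about 17 of 200.

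**Step 6. Women with neither a call nor a full record window.** If the 75% complete follow-up assumed in Sample size considerations applied to the call (my assumption, since the article does not say so), 25% of the 31 women in step 1, about 8, would have neither.

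Steps 1 to 5 concern the EMR and CRF sources only. The call is timed from each inclusion and is unaffected by the visit date.

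**The case against.** The strongest reply is that the article never says follow-up stops at the visit. It requires the search to run to day 28, and no visit date relative to the last inclusion is given. The phrase about the end of recruitment could simply mean a close-out visit, with exact scheduling left to operational documents. The record review is also a secondary source: the diary, the call and the practice CRFs come first.

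Much of this stands. The call at day 28 covers symptoms, antibiotic use, recurrences and reconsultations for every woman, late enrollees included. Nothing says that CRFs written after the visit are discarded. Upper UTI could also surface through the clinical features on a reconsultation CRF, or through the call's questions on symptoms and reconsultations.

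What does not stand is that the coverage requirement settles the timing. The 6 months given in brackets are the recruitment period, and the Table 1 footnote ties the review to the end of enrolment at each practice. The position of that column after the day-28 column does not imply a lag: the day columns count from each woman's enrolment, whereas the last column is an event of the practice. A team following the text would visit when enrolment closes.

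A reader might go further and infer any of three things, none of which the document supports:

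- **Overall follow-up of late enrollees is truncated.** It is not, because the call is independent of the visit.
- **The retention endpoint is affected.** Primary objective defines retention as complete follow-ups per site over 28 days and does not tie it to the visit or the record review.
- **The shortfall differs by arm**, for example because the 3-month refresher training changes accrual. The article says nothing about accrual by arm.

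**Conclusion.** The point holds as a conflict between the stated visit time and the stated coverage. Read literally, the record check and follow-up CRF collection would be incomplete for about 15% of women (31 of 200), amounting to about 7.7% of 28-day person-time and 11.5% of day 15–28 person-time in those sources. These figures assume uniform accrual over 6 months and a visit on the closing day, and they fall to zero if the visit is at least 28 days later. The exposure is confined mainly to upper UTI, prescription counts and defined daily doses after the diary ends, and the back-up for women missed by the call.

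Severity is moderate to minor. The outcomes concerned are secondary and exploratory in a pilot that its authors say is not powered for effects, and the call covers much of the same ground.

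**What to change.** State in the electronic records paragraph that the outreach visit, CRF collection and record review take place at least 28 days after the last inclusion at each practice. Change the last column of Table 1 and its footnote to match. Preferably, add an upper-UTI item to the existing day-28 call, so that this endpoint does not rest on the record review alone.

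The cost is that site visits and data lock move about 4 to 5 weeks later, and one question is added to a call already planned. No extra visits or staff are needed. The article reports recruitment as ongoing, so the change was still possible at that stage.

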#### Control arm–usual care

Practices in the control arm will not necessarily have their management guided by POCTs. They will perform usual care. The treatment decision is usually based on symptoms. Dipsticks for detecting erythrocytes, leucocyte esterase or nitrites can be added in case of diagnostic uncertainty.^33^ Procedures are the same as those outlined above, except for POCTs: microscopy only pertains to the intervention arm.

Table 1 and figure 2 summarise trial procedures.

**Table 1 T1:** Schedule of Microscopy in Urinary Tract Infections trial procedures according to the Standard Protocol Items: Recommendations for Interventional Trials guideline^40^

Time point (day 0=patient enrolment) procedures	<0	Day 0 Baseline	Day 1–7	Day 28	End of patient enrolment*
Enrolment:					
Practice recruitment	X				
Randomisation	X				
Allocation	X				
Training	X				
Screening for potential inclusion		X			
Formal eligibility assessment		X			
Intervention:					
Baseline consultation†		X			
POCTs‡		X			
Urine sent to laboratory†		X			
Assessments:					
Practice size	X				
Paper-based CRF§		X			
Patient diary¶			X		
Follow-up telephone calls				X	
EMR review**					X

*End of patient enrolment in each practice.

†Applies to intervention and control arm practices.

‡Applies only to intervention arm practices.

§In case of reconsultation for UTI on days 1–28, paper-based follow-up CRFs are used.

¶Follow-up on days 1–7 or up to day 14 if symptoms last longer or recur.

**Follow-up on days 1–28 (CRF completeness and accuracy check).

CRF, case report form; EMR, electronic medical records; POCT, point-of-care test; UTI, urinary tract infection.

**Figure 2 F2:**
[figure not shown]
Flow diagram of the Microscopy in Urinary Tract Infections trial procedures. BayFoNet, Bavarian Practice-Based Research Network; CRF, case report form; GP, general practitioner; POCTs, point-of-care tests.

#### Microbiological analyses

For cultural urine diagnostics, at each study site, medical assistants immerse a dipslide, that is, a culture medium carrier (Uricult Plus, Roche Diagnostics GmbH, Mannheim, Germany) into the test urine until the agar surface is completely covered. After removal from the urine, the carrier is placed into a sterile transport tube for transportation via post to the IHM. On arrival, the carrier is incubated at 35±2°C for 16–24 hours. If bacterial growth is detected, the subsequent analysis is carried out according to the established diagnostic procedures of the accredited medical laboratory. Briefly, the analysis includes the determination of the overall bacterial count on the Cystine Lactose Electrolyte Deficient–agar plates, and those of gram-negative bacteria (on MacConkey agar plates) and of *Enterococcus* spp (on the *Enterococcus* agar plates). Bacteria are subcultured on Columbia Sheep Blood agar plates and MacConkey agar plates to be subsequently identified by mass spectrometry (VITEK MS, BioMérieux, Marcy-l’Etoile, France). Susceptibility testing of pathogenic bacteria is achieved using VITEK 2 (BioMérieux, Marcy-l’Etoile, France) and interpreted according to the European Committee on Antimicrobial Susceptibility Testing (EUCAST) criteria.^35^

To define a significant growth in the MSU specimens, the criteria specified in the updated 2020 German infectious disease and microbiology laboratory quality standards will be used.^30^

